### 2.9. Ethical Considerations

This is a non-blinded, interventional, multicenter, single-arm trial designed to evaluate the clinical benefits of RST-guided management in patients with chronic heart failure. The study has been registered with jRCT (registration number: jRCTs042240196) and will be conducted in accordance with the Declaration of Helsinki and the International Conference on Harmonization Good Clinical Practice guidelines. The ethical aspects of the study plan, protocol, and informed consent process have been approved by the Clinical Research Review Board, University of Toyama (SCR2024002) on 29 January 2025 prior to the commencement of the study. All participants will provide written informed consent before being enrolled in the study.

## 3. Expected Results

We anticipate that the ITMETHOD-HF-III study will demonstrate that mandatory, RST-guided heart failure management significantly reduces the incidence of the primary composite endpoint—heart failure hospitalization and cardiac death—compared with symptom-guided standard care in the historical control group (ITMETHOD-HF-II). Specifically, we expect that the implementation of early therapeutic interventions triggered solely by RST alerts, irrespective of clinical signs or symptoms, will enable the timely optimization of pharmacologic therapy and effectively prevent clinical decompensation.

It is projected that patients receiving RST-guided management will show a lower cumulative incidence of first heart failure hospitalization and cardiac death over the 1.5-year follow-up period. Moreover, secondary analyses are expected to reveal that the magnitude and trajectory of RST recovery following intervention will correlate with improved clinical outcomes, while persistent low RST values despite treatment may identify patients at elevated risk for adverse events. In particular, we expect that patients who achieve an RST increase to ≥30 s within 14 days after the alert threshold will exhibit favorable prognoses.

Feasibility assessments are expected to confirm the reliability and clinical usability of the automated, contactless RST monitoring system in real-world outpatient settings. We also anticipate that the study will validate the prognostic utility of RST as a non-invasive surrogate for pulmonary congestion and subclinical hemodynamic deterioration.

If the results support our hypothesis, this study will provide the first evidence that mandatory therapeutic intervention based solely on RST alerts can reduce heart failure events, thereby establishing a novel, scalable paradigm for telemonitoring-guided care in chronic heart failure management. Whether such an improvement of clinical outcomes by the RST-guided management may improve the cost-effectiveness of heart failure management remains a future concern.

## 4. Discussion

The innovative technology developed by our team facilitates the comprehensive measurement of overnight physiological variables in a fully automated manner, eliminating the need for attaching or implanting biological sensors onto patients. A sheet-type sensor continuously monitors and records respiratory patterns throughout the night. The acquired data undergoes complete automated processing and is transmitted to a cloud server via the Internet, where all-night RST is computed each morning.

In this ITMETHOD-HF-III study, the aim is to evaluate the clinical significance of RST-guided management in reducing hospitalization rates and mortality associated with heart failure, compared with conventional symptom-guided management strategies. Notably, this approach “mandates” the up-titration of heart failure medications in patients whose RST falls below a predefined threshold, regardless of the presence or absence of overt heart failure symptoms (probably absence in many cases).

### 4.1. How to Detect Sub-Clinical Worsening Heart Failure

Worsening heart failure typically begins with an increase in intracardiac filling pressures [20]. Such increases are often detectable several weeks before the emergence of overt signs and symptoms of heart failure. To monitor these initial and sometimes trivial changes, direct daily measurement of pulmonary artery pressure using wireless implantable monitoring devices has been used [12]. For instance, the CHAMPION trial demonstrated that heart failure management guided by wireless pulmonary artery hemodynamic monitoring effectively reduced heart failure hospitalizations through timely adjustments of medications [13]. However, these devices are hindered by significant drawbacks, including their invasiveness and substantial medical costs.

Our technology for calculating RST values addresses these limitations through its non-invasive nature, affordability, and broad applicability, maintaining predictive accuracy [15]. Within the human lung, the progression of pulmonary congestion is inherently monitored by four built-in sensor systems, particularly the vagal nerve collagen sensors. The irritant vagal afferents activated by lung stretch reflexes respond to pulmonary congestion by exerting counteracting effects on respiratory patterns, leading to respiratory instability. In addition, increased central blood volume mechanically restricts lung inflation, resulting in rapid and shallow breathing. Consequently, elevated cardiac filling pressures and central blood volume can be reliably inferred from decreases in RST values, well before the clinical manifestation of heart failure.

Supporting this, prior studies have shown that an RST decrease below 20 s was a robust predictor of future heart failure hospitalization, with detection occurring up to three weeks prior to clinical onset [19].

### 4.2. Rationale for the Inclusion/Exclusion Criteria

Optimal patient selection is essential for the effectiveness of RST-guided management. The primary goal of this intervention is to prevent hospitalizations due to heart failure. Patients with a heightened risk of hospitalization are ideal candidates for RST-guided management, whereas those with minimal risk may not derive significant benefit from such monitoring [21]. Therefore, the inclusion criteria require participants to have a documented history of at least two prior hospitalizations for heart failure.

Conversely, patients with advanced or refractory disease may not be suitable for RST-guided management, since their conditions are less likely to respond to any therapeutic adjustments [22]. To address this, we exclude individuals receiving durable left ventricular assist devices, as well as those with persistently low RST values below 20 s, which signify severe and unresponsive respiratory instability.

In addition, patients with conditions that could confound RST measurements or limit their applicability are excluded. These conditions include sleep apnea syndrome, advanced pulmonary diseases, and prior stroke [19]. Though these exclusion criteria are necessary to maintain the integrity of the study, they also highlight the current limitations of RST in certain patient populations.

### 4.3. How to Demonstrate the Clinical Implication of RST-Guided Management

Evidence from previous studies suggests that a decrease in RST below 20 s can predict heart failure hospitalization up to 28 days in advance [19]. However, the clinical efficacy of aggressive therapeutic interventions to prevent such hospitalizations in real-world daily practice remains uncertain.

In the ITMETHOD-HF-II trial, patients were encouraged to be admitted when their RST fell below 20 s. However, therapeutic decisions, including the up-titration of heart failure medications, were left to the discretion of attending physicians. In many cases, medications were not adjusted, likely because patients were asymptomatic due to early hospital admission. To unequivocally demonstrate the utility of RST in identifying subclinical heart failure and preventing hospitalizations, “mandatory” up-titration of heart failure medications is essential when RST values fall below this threshold.

Findings from the ITMETHOD-HF-II study reinforce this approach. All patients who achieved RST values of ≥30 s within 14 days by therapeutic intervention successfully avoided heart failure hospitalizations. This is a rationale why we set 30 s of RST as a therapeutic target. Based on these findings, we strongly propose repeating therapeutic adjustments until RST values exceed 30 s.

However, mandatory interventions carry potential risks, particularly in patients with hypovolemia or renal impairment, in whom hemodynamic instability may occur. Therefore, careful risk-benefit analyses are crucial to ensure the safety of mandatory interventions, especially in asymptomatic patients.

It is also important to recognize that not all participants may experience an increase in RST despite aggressive therapeutic interventions. A thorough assessment of patient characteristics, the types of interventions attempted, and clinical outcomes is necessary to identify refractory cohorts. These findings will help inform the development of tailored therapeutic strategies for these populations in future studies.

### 4.4. Study Limitation

This study protocol has several limitations that warrant consideration. First, the ITMETHOD-HF-III study is designed as a single-arm, non-randomized trial utilizing a historical control group from the previous ITMETHOD-HF-II study. Although this approach facilitates rapid implementation and comparative analysis, it inherently limits the ability to control for unmeasured confounders and time-dependent biases such as changes in clinical practice, therapy use, and healthcare delivery. Differences in clinical practices, patient management strategies, or healthcare delivery systems between the two study periods may influence outcomes independently of the intervention itself. We may add propensity score analysis to further address residual confounding.

Second, the protocol mandates therapeutic up-titration solely based on RST values, irrespective of heart failure symptoms or physical findings. While this strategy aims to validate the utility of RST in detecting subclinical deterioration, it also introduces a potential risk of overtreatment, particularly in patients with borderline RST values or comorbidities such as renal dysfunction or hypovolemia. Final decision to strengthen the therapy, including the up-titration of diuretic dose, is at the discretion of the attending physicians. The response of RST values to each therapeutic intervention also remains a concern to be analyzed. The safety and tolerability of such aggressive, symptom-independent interventions remain to be fully established.

Third, RST measurement relies on a piezoelectric sensor and proprietary algorithm, which, although validated in previous studies, may be influenced by factors such as sleep position, body movement, and comorbid pulmonary or neurological conditions. We defined several stringent inclusion and exclusion criteria to mitigate these confounders. Conversely, such strict criteria may limit generalizability to real-world clinical management. Further studies are warranted to evaluate the applicability of this system and our therapeutic strategy utilizing this technology.

Fourth, due to the open-label, single-arm design, neither participants nor clinicians are blinded to the intervention, which may introduce bias in outcome ascertainment and therapeutic decision-making. Although outcome adjudication is performed in a blinded manner by an independent committee, the potential for performance and detection bias cannot be fully excluded.

Fifth, as the present manuscript is a study protocol, baseline demographic, clinical, and instrumental characteristics—such as comorbid conditions, risk factor profiles, and heart failure phenotypes—are not yet available and thus not presented. These parameters are known to affect prognosis, therapeutic responses, and risk of heart failure readmission. We will thoroughly incorporate these data and adjust them, if applicable, in subsequent publications upon study completion.

Sixth, the sample size calculation was based on an anticipated 50% reduction in the event rate, which may be relatively optimistic. Although this assumption was informed by the early predictive performance of RST observed in prior studies—comparable to or exceeding that of invasive monitoring technologies such as CardioMEMS—we acknowledge that the actual effect size may be smaller. The results of this study will provide critical data for refining effect size estimates and conducting sensitivity analyses in future confirmatory trials.

Lastly, although the study design includes frequent follow-up and protocolized management pathways, patient adherence to outpatient visits following RST alerts is critical. Delays or non-compliance in clinic attendance may reduce the effectiveness of the intervention and confound outcome assessment.

Despite these limitations, the ITMETHOD-HF-III study represents an important step toward validating a novel, non-invasive, and scalable tool for the early detection and management of worsening heart failure in the outpatient setting.

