**Figure 1 jcm-14-04653-f001:**
[figure not shown]
Methodology to calculate RST values (reused with permission) [18]. All spectral power is normalized by the power spectral density or the ratio of the maximum power of the components. All respiration frequency points with a power spectral density > 10% are equally adopted in the assessment of respiratory instability. Very low-frequency points of the periodic breathing curve are only adopted if the power spectral density of the very low-frequency component is >50% of the maximum power of the respiratory component. Respiratory frequency points are evaluated using standard deviation, and RST value is defined as the inverse of the standard deviation. CSR, Cheyne–Stokes respiration; Resp, respiration; RST, respiratory stability time.

Building on these findings, a multicenter, prospective study, **Innovative Tele-Monitoring Environment To Halt Ongoing Deterioration of Heart Failure-I (ITMETHOD-HF-I)**, was conducted from 2017 to 2019 [19]. This study used an upgraded RST monitoring system and identified an RST threshold of 20 s as the optimal cut-off for predicting future heart failure-related hospitalizations.

Subsequently, the **ITMETHOD-HF-II trial**, a multicenter, prospective, randomized, controlled study, evaluated the clinical utility of prospective RST monitoring. Patients were advised to visit outpatient clinics if their RST fell below 20 s, although the decision to adjust medications was left to the discretion of the attending physicians. Clinical decisions eventually relied on traditional signs and symptoms assessed during outpatient visits despite continuous RST monitoring.

To fully elucidate the clinical implications of RST-guided management, particularly its potential to detect “occult” heart failure progression before symptom onset, give us a chance to enhance heart failure medications, and prevent worsening heart failure, therapeutic intervention must be systematically aligned with RST alerts “alone”, irrespective of heart failure signs/symptoms. The current **ITMETHOD-HF-III study** addresses this gap by “mandating” the up-titration of heart failure medications whenever RST reaches the alert threshold, irrespective of clinical signs or symptoms. This single-arm, multicenter, prospective study will compare outcomes, including heart failure hospitalizations and cardiac mortality, against those observed in ITMETHOD-HF II, where medication adjustments were discretionary.

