### 2.2. Study Design

After obtaining informed consent, patients will undergo a screening process to determine their eligibility (Figure 2). Eligible patients will be enrolled in the primary registration phase, during which the telemonitoring system will be set up, and initial RST measurements will be conducted. Upon verification of accurate RST measurements, patients will progress to secondary registration. At this stage, RST-guided management will start.

Clinical parameters, including RST values, will be continuously monitored over a 1.5-year observation period. The historical control group will consist of participants from the prior **ITMETHOD-HF II trial**, in which RST values were monitored, but therapeutic decisions were left to the discretion of attending physicians. In contrast, the current study “mandates” therapeutic interventions whenever RST values fall below the alert threshold, irrespective of clinical signs or symptoms.

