### 2.4. RST-Guided Management

Therapeutic intervention is initiated by up-titrating heart failure medications when daily RST meets either of the following alert thresholds for two consecutive days, irrespective of the presence of heart failure symptoms: (1) the RST value falls below 20 s for two consecutive days; or (2) the average RST value remains above 45 s for over one month but then decreases progressively to below 30 s within a period of 10 to 90 days. A visual decision tree outlining the RST alert criteria and subsequent actions is summarized in Figure 6.

Patients are instructed to visit the outpatient clinic within three business days when their RST reaches the alert threshold. If, despite therapeutic intervention, the RST does not improve to exceed 30 s, patients will be asked to revisit the outpatient clinic for further evaluation and intensification of treatment. This process will be repeated as necessary until the RST stabilizes above 30 s. Management will continue to ensure sustained improvement in RST levels.

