### 2.5. Study Visits and Follow-Up

Following informed consent and initial screening, patients are enrolled in the primary registration. During screening, data are collected on heart failure symptoms, vital signs, chest X-ray, electrocardiogram, laboratory parameters (plasma B-type natriuretic peptide or serum NT-pro B-type natriuretic peptide, hemoglobin, serum creatinine, and blood urea nitrogen), transthoracic echocardiography, and medication history (Table 2). On confirmation of appropriate RST measurement, patients are included in the secondary registration, and RST-guided management is started.

Throughout the 1.5-year observation period, patients are monitored at the outpatient clinic at regular intervals, typically once per month. Clinical data collected at each visit are recorded when available. In the event of hospitalization due to low RST, chest X-ray and laboratory tests are mandatory, and the dosage of heart failure medications is systematically up-titrated, regardless of the presence of heart failure symptoms.

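### Section 4.4 gives the attending physician an unconditioned final say on strengthening therapy, while sections 2.2, 2.4 and 2.5 make up-titration mandatory, so the article does not settle which rule governs at an RST alert

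*Protocol article*

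**What the plan says.** **The rule for this study.** Section 2.2 says that the current study mandates "therapeutic interventions whenever RST values fall below the alert threshold, irrespective of clinical signs or symptoms". Section 2.4 makes it operational: "Therapeutic intervention is initiated by up-titrating heart failure medications when daily RST meets either of the following alert thresholds". If RST does not rise above 30 s, the patient returns for further intensification, and this repeats until RST is stable above 30 s. Section 2.5 adds that, in a hospitalization due to low RST, "the dosage of heart failure medications is systematically up-titrated, regardless of the presence of heart failure symptoms". None of the three sections gives the physician an opt-out.

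**The rule for the control.** Section 1 describes ITMETHOD-HF-II, where the threshold was 20 s. On attendance it says: "Patients were advised to visit outpatient clinics if their RST fell below" that value. On treatment it says: "although the decision to adjust medications was left to the discretion of the attending physicians". Section 4.3 says the same: "therapeutic decisions, including the up-titration of heart failure medications, were left to the discretion of attending physicians". It adds that drugs were often left unchanged, probably because the patients had no symptoms.

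**Section 4.4.** The second limitation begins by restating the mandate: "the protocol mandates therapeutic up-titration solely based on RST values, irrespective of heart failure symptoms or physical findings". The next sentence warns of overtreatment. The one after it reads: "Final decision to strengthen the therapy, including the up-titration of diuretic dose, is at the discretion of the attending physicians".

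**The concern.** One decision, whether to intensify treatment at an alert, is obligatory in the Methods and left to the physician in section 4.4. This matters more than an ordinary wording slip because physician discretion is the feature of ITMETHOD-HF-II that the new study sets out to replace. Advice to attend when RST fell below 20 s was already part of ITMETHOD-HF-II, so attendance alone does not separate the two groups. What follows the alert does.

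If physicians use the discretion beyond safety grounds, the two policies move closer together and any difference most likely shrinks toward none. Interpretation suffers in either direction. A null result could mean that the strategy failed or that it was not delivered. A positive result would support an alert combined with physician judgement, whereas section 3 plans to claim first evidence for obligatory treatment triggered by RST alerts alone, and section 5 stresses that the obligation is necessary.

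**Working it through.** No figure in the plan is in dispute, so the check sets the rules side by side and asks what each requires in concrete cases.

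| Situation | Sections 2.2 and 2.4 | Section 4.4, final-decision sentence |
|---|---|---|
| Alert, no symptoms, no safety problem | Up-titrate; absence of symptoms is no ground to decline | Physician decides; no ground is excluded |
| Alert, patient hypovolemic or with renal dysfunction | Up-titrate; no exception stated | Physician may withhold |
| Alert, RST only just below the threshold | Up-titrate; the threshold is the rule | Physician may withhold |
| Revisit, RST still not above 30 s | Intensify again | Physician may decline |

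**Step 1: do the rules conflict?** In every row the Methods require action and section 4.4 permits inaction. For the first row the mandate restated in section 4.4 points toward treating, but the final-decision sentence sets no limit of its own. No sentence says which rule prevails.

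**Step 2: does the context resolve it?** Partly. The final-decision sentence directly follows the overtreatment warning, which names renal dysfunction and hypovolemia, and section 4.3 asks for risk-benefit analysis before mandatory treatment of asymptomatic patients. That points to a safety override. But the warning also names borderline RST values, and declining on that ground would work against the threshold itself. The sentence also covers strengthening therapy in general, of which diuretic dose is only one part.

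**Step 3: how close is this to the control policy?** The section 4.4 wording for the new study and the section 4.3 wording for ITMETHOD-HF-II both leave the decision, including up-titration, to the attending physician's discretion. Two elements of the new policy still differ from ITMETHOD-HF-II as the article describes it: the second alert (a fall from above 45 s to below 30 s) and the loop of repeated intensification until RST exceeds 30 s. Both take effect through a decision to intensify, so both also depend on which rule governs that decision.

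**Step 4: can the loss be sized?** No. It would need the share of alerts acted on in each cohort. Section 4.3 gives no proportion for ITMETHOD-HF-II, and nothing is stated for the new study. Section 2.7 assumes that RST guidance halves the admission rate (43.1% × 0.5 = 21.55%, stated as 21.6%) without saying what share of alerts must be acted on to achieve this.

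**The case against.** The strongest reply is that there is no contradiction, only a mandate with an ordinary clinical safety override. On this view the Methods remove one ground for not treating, the absence of signs or symptoms. They do not oblige anyone to treat against a contraindication, and the disputed sentence sits beside the overtreatment warning. Much of this stands. A safety override is probably what was meant, and it should be kept. But section 4.4 states the mandate as applying irrespective of physical findings as well as symptoms, and the sentence that follows carries no safety condition.

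A second reply is that the sentence stands among the limitations, and that criteria for withholding treatment belong in the full protocol, which is not shown. That also stands in part: the point is not that such criteria are missing. It is that the published text gives two rules for one decision. If the full protocol resolves this, a pointer to it would do.

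A third reply is that the new policy differs from ITMETHOD-HF-II in more than the mandate. That is correct, and the point is limited accordingly.

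Three stronger readings are not supported:

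- A reader might infer that the study simply repeats the control policy. It does not: absence of symptoms is ruled out as a reason to decline, and the second alert and the 30 s loop remain.
- A reader might attach a power loss to the discretion. Any such figure would rest on an invented share of alerts acted on.
- A reader might take the Change row of Table 2 as requiring a change of treatment at the alert visit. The table schedules data collection, so it does not settle whether treatment must change.

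**Conclusion.** The point holds as an inconsistency that should be fixed. Up-titration at an RST alert is mandatory in the Methods and discretionary in section 4.4, the discretion is not tied to safety, and discretion is the feature that defines the historical control. The main contrast, though not the only one, is therefore left open, and the conclusion planned in section 3 may describe a policy other than the one delivered.

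The size of any dilution is unknown and cannot be derived from the article. The expected direction, toward no difference, assumes that discretion is in fact used beyond safety grounds; the article does not show that it will be. If physicians withhold only for genuine safety reasons, the remaining problem is mainly one of wording and reporting.

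**What to change.** Reword the final-decision sentence in section 4.4, for example: up-titration is mandatory at each RST alert; the attending physician may withhold or limit it only for a safety reason, such as hypovolemia or renal dysfunction, recorded at that visit, and never because heart failure symptoms are absent. The list of reasons is the sponsor's clinical decision. If the full protocol already holds it, a reference is enough.

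Three additions follow, offered as proposals and not as a claim that the unseen documents lack them:

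- Record the reason whenever treatment is not intensified at an alert visit, or at a revisit with RST not above 30 s. Table 2 already schedules collection of treatment change at the alert visit, and at the revisit if implemented, so the reason is the new item.
- Report the proportion of alerts acted on beside the primary result.
- Word the section 3 conclusion for the policy actually delivered.

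The cost is one sentence, one data item per alert visit or revisit without intensification, and one descriptive table. Physicians keep the freedom to protect a patient at risk.
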